### Statistics

The mean Global Health Status (GHS) in our population has been esteemed to 37.5 ± 10.4 [29] or 39 ± 26 [30]. Considering a standard deviation equal to 26 under the hypotheses that (i) the variance of the GHS score at inclusion and at day 56 are equal, and that (ii) the correlation between the score at day 0 and day 56 is equal to 0.5, and expecting a clinically significant change in the GHS of 8 points between day 0 and day 56, we calculated that 167 participants are needed in each group for an 80% study power. Considering the high risk of attrition in our population, we increased by 20% the number of participants needed, resulting in a total number of patients needed to 418 participants.

Analyses will be performed in intention to treat. The intention to treat population will be defined as all patients included in the study, regardless if they are assessed for the primary outcome or not. A modified intention to treat population will be defined as the intention to treat population without participants deceased before the end-point or for whom the primary outcome is missing.

Analyses will be performed using the SAS 9.4 software (SAS Institute Inc., Cary, NC, USA), considering an alpha-risk of 0.5.

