### Sample Size

Based on an expected standard deviation of 26 in our primary outcome (The Global health Status), and considering a correlation of 0.5 between inclusion and day 56 (corresponding in a standard deviation of the variation of the GHS score of 26 between baseline and day 56), and expecting a moderately clinically significant difference of 8 points between groups, it will be necessary to include 418 participants (bilateral test, alpha risk of 0.05, power of 0.8, attrition 0.2).

Considering the risk of lost to follow-up due to our population global condition, we considered an attrition rate of 20% when calculate the sample size.

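### The Statistics section sets the significance level for the analyses at 0.5, while the trial was sized for a two-sided 0.05

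*Protocol article*

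**What the plan says.** Two sections of the protocol article give an alpha.

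- **Statistics**, closing sentence, on how the analyses will be carried out in SAS: "considering an alpha-risk of 0.5". It gives no sidedness and is not limited to any one outcome.
- **Sample Size**, on the calculation for the primary outcome: "bilateral test, alpha risk of 0.05, power of 0.8, attrition 0.2", with the target given as "expecting a moderately clinically significant difference of 8 points between groups".

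The Statistics section also reports the result of the sample size calculation, "we calculated that 167 participants are needed in each group for an 80% study power", and the inflated total, "resulting in a total number of patients needed to 418 participants". It does not repeat the alpha used to get there. The sentence with 0.5 is therefore the only one that sets a level for the analyses, as distinct from the sample size.

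**The concern.** The significance level is the rule by which the trial will be declared positive or negative, and the article gives two values that differ tenfold. A reader who consults only the Statistics section gets the wrong one.

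If that section were followed as written, half of all comparisons with no true difference would be called significant. This applies to the primary comparison of the Global Health Status (GHS) and to each secondary outcome that is tested statistically. The interview-based outcome is not affected, because no significance test applies to it. The 80% power statement would also describe a different test from the one being run.

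A clear threshold fixed in advance matters particularly here, because the trial is open-label and relies mainly on patient-reported outcomes.

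**Working it through.** **Inputs**

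- SD of the GHS: 26 (Sample Size: "Based on an expected standard deviation of 26 in our primary outcome (The Global health Status").
- Correlation between baseline and day 56: 0.5 (Sample Size and Statistics).
- Difference to detect between groups: 8 points (Sample Size).
- Power 0.80, attrition 20%, two-sided alpha 0.05 (Sample Size).
- Alpha for the analyses: 0.5 (Statistics).

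**1. SD of the change score**

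sqrt(26² + 26² − 2 × 0.5 × 26 × 26) = 26. This agrees with the article: "corresponding in a standard deviation of the variation of the GHS score of 26 between baseline and day 56".

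**2. Reproducing the article's sample size at a two-sided 0.05**

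- Normal approximation: n per group = 2 × [26 × (1.960 + 0.842) / 8]² = 165.8, so 166.
- t-test version: 166.8, so 167, which is the stated figure.
- Attrition: 167 / 0.8 = 208.75, so 209 per group and 418 in total, which is the stated total.

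**3. Trying other alphas with the same inputs**

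| Alpha | n per group before attrition |
|---|---|
| two-sided 0.05 | 166 (normal), 167 (t-test): matches |
| one-sided 0.05 | 131 (normal) |
| two-sided 0.5 | 49 (normal), 46 (t-test, 45.07 rounded up) |

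At 0.5 the two methods differ slightly because the t-test routine also counts rejections in the wrong direction, which are not negligible at so loose a level. Neither figure is near 167.

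**4. What 0.5 would mean for the analysis, with 167 evaluable per group (normal approximation)**

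Standard error of the between-arm difference = 26 × sqrt(2/167) = 2.845 points. The expected z at 8 points is 8 / 2.845 = 2.81.

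| | alpha 0.5 | alpha 0.05 |
|---|---|---|
| Critical value of \|z\| | 0.674 | 1.960 |
| Smallest significant difference | 0.674 × 2.845 = 1.9 points | 1.960 × 2.845 = 5.6 points |
| Type I error per test | 50% | 5% |
| Power at 8 points | 98.4% | 80.3% |

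The smallest significant difference at 0.5 is 1.9 / 8, or about a quarter of the difference the trial was sized to detect.

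**The case against.** The best reply is that this is plainly a typing error. The Sample Size section gives 0.05, the article's own figures reproduce only at 0.05, and nothing else suggests that anyone plans to test at 0.5. On this view the 50% error rate belongs to the literal text and not to the trial, and the point is editorial. The Sample Size section could also be read as fixing the alpha of the primary test already.

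Much of this stands. The slip is recognisable, the design is unaffected, and the authors very probably intend 0.05. It does not remove the point. The Sample Size section states the alpha used to calculate N, and the sentence that governs the analyses states another value. The wrong number sits on the decision rule, not in background text. That an article condenses a fuller document, or that an analysis plan may exist, can excuse an omission but not a wrong statement.

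One limit applies to clinical comparisons. The Outcomes assessment section calls a GHS difference of 4 to 8 points small, but defines that range for change from baseline to day 56. The 1.9 points is a between-arm figure, so setting it below that range is only indicative. The finding does not depend on it.

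**Conclusion.** The concern holds. The article contradicts itself on the significance level, and the value in the Statistics section is the wrong one, since 167 per group and 418 in total require a two-sided 0.05. Read literally, the rule raises the false-positive rate per test from 5% to 50% and lowers the smallest significant difference from about 5.6 to about 1.9 GHS points.

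The figures in points and the power values assume the article's own SD of 26 for the change score, 167 evaluable patients per group and a simple two-group comparison of mean change. The 50% follows from the definition of alpha and needs none of these assumptions. The sample size is sound on this point. Whether the full protocol or an analysis plan carries the same slip cannot be seen from the article.

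**What to change.** In the Statistics section, replace the alpha of 0.5 with a two-sided alpha of 0.05, in agreement with the Sample Size section, and state the sidedness there as well. Check the full protocol and any statistical analysis plan for the same slip, and correct it wherever it appears before the analysis begins.

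The cost is one corrected number and a published correction to the article. The total stays at 418, power stays at about 80% with 167 evaluable per group, and no trial procedure changes.

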### Qualitative part procedure

We will perform a qualitative comparative analysis of semi-structured interviews.

Only patients from the coordination center will be offered to take part in this sub-study.

### Legal and administrative considerations

The current protocol has been approved by the Committee for Persons Protection Sud Est I. On the 17/12/2020 with reference MEDAECPP-2020–10-00,020.

The study fulfilled all administrative requirements for clinical trials under the French law.

No data monitoring committee will set up. The sponsor will handle data monitoring twice a year for the time of the study and following the French legal requirements.

The study design complies with the Consolidated Standards of Reporting Trials (CONSORT) statement, and the current protocol complies with the Standard Protocol Items: Recommendations for Interventional Trials (SPIRIT) [31].

## Discussion

If mirtazapine is proven to be efficient in improving patients’ quality of life, independently of its antidepressant effect, in advanced cancer poly-symptomatic patients would constitute a major progress. Additionally, this study might highlight target symptoms that could be relieved using mirtazapine and potential target symptom clusters.

This could allow limiting polypharmacy in advanced cancer patients by offering a new therapeutic option well tolerated in this frail population. Additionally, this would mitigate the risk of adverse event and drugs interaction in this population often affected by polypharmacy due to numerous conditions and symptoms. This would constitute a major step for patients’ security. As mirtazapine is a very cheap drug, this would also contribute in limiting health care expenditures.

Besides limiting polypharmacy, several symptoms have very limited therapeutic options currently available. This is the case for cancer anorexia. Few drugs, including megestrol acetate and corticoids, have been proven to be effective in improving appetite. However, they have important side effects, limiting their use in the overall advanced cancer population. As mirtazapine is expected to be well tolerated, any effectiveness sin improving appetite might open an interesting therapeutic way for anorexia in advanced cancer.

For breathlessness treatment, no drug is currently licensed in the European Union. Morphine has been evaluated many times, but its effectiveness is still under debate. King’s College London recently launched an ambitious project aiming to assess the effectiveness of mirtazapine in alleviating breathlessness in chronic lung disease [32]. Results from this wide UK randomized control trial and form our study could motivate considering licensing mirtazapine in treating this symptom.

Additionally, mirtazapine is available in many countries under the shape of orodispersible tablets. This galenic form ensures its use for most cancer patients, including those who have swallowing disorders, intestinal obstruction or any other contraindication for oral intakes, while limiting venous access when not necessary.

Beyond the potential benefits to the patients and public health this study will inform further researches by providing information on advanced cancer patients’ quality of life, their experience of polysymptomatology and polypharmacy. This will also provide information on further researches on mirtazapine. Finally, feedback from this mixed-method randomized-controlled trial will provide useful information to subjective and objective aspects of research in palliative care patients’ quality of life, and thereafter suggests future methodological improvements.

### Limitations

For practical reasons, the current trial will be an open-trial. A recent modification in grading the evidence does not inevitably consider open-labeled trials as subject to important biases. Despite this new grading system, a blinded trial would have probably provided better evidence. To avoid biases, analyses, including qualitative analyses, will be performed by blinded researchers [33]. In this purpose, the researcher that will transcribe the semi-structured interviews verbatim will remove any identifiable data in the verbatim and blind them for randomization arm. This researcher will not take part in qualitative analyses.

## Data Availability

The current protocol is labeled by the number NCT04763135 on ClinicalTrials.gov. The current protocol is labeled by the number 2020–002,994-90 on the European Union Drug Regulating Authorities Clinical Trials Database. Other data are available upon reasonable request to the corresponding author.

## Abbreviations

ASEC: Antidepressant Side-Effect Checklist
CCS: Canadian Cancer Society
CTCAE V4.0 / CTACAE: Common Terminology Criteria for Adverse Events Fourth Version
ECG: Electrocardiogram
EORTC QLQ-C30 / QLQ-C30: European Organisation for Research and Treatment of Cancer Quality of Life Questionnaire 30
ESAS 12F: Edmonton Symptom Assessment Scale 12 French
ESMO: European Society for Medical Oncology
GHS: Global Health Status
HRQoL: Health-Related Quality of life
MADRS: Montgomery-Åsberg Depression Rating Scale
HADS-D: Hospital Anxiety and Depression Scale—Depression
MARS: Medication Adherence Report Scale
